## Abstract

**Background:**

Sorafenib is an oral multikinase inhibitor with antiangiogenic/antiproliferative activity. A randomized phase 2b screening trial in human epidermal growth factor receptor 2 (HER2)-negative advanced breast cancer demonstrated a significant improvement in progression-free survival (PFS) when sorafenib was added to capecitabine versus placebo (median 6.4 versus 4.1 months; hazard ratio = 0.58; *P* = 0.001). Most drug-related adverse events were Grade 1/2 in severity with the exception of Grade 3 hand-foot skin reaction/syndrome (44% versus 14%, respectively). These results suggest a role for the combination of sorafenib and capecitabine in breast cancer and supported a phase 3 confirmatory trial. Here we describe RESILIENCE - a multinational, double-blind, randomized, placebo-controlled, phase 3 trial - assessing the addition of sorafenib to first- or second-line capecitabine in advanced HER2-negative breast cancer.

**Methods/design:**

Eligibility criteria include ≥18 years of age, ≤1 prior chemotherapy regimen for metastatic disease, and resistant to/failed taxane and anthracycline or no indication for further anthracycline. Prior treatment with a vascular endothelial growth factor inhibitor is not allowed. Patients with significant cardiovascular disease or active brain metastases are not eligible. Patients are stratified by hormone-receptor status, geographic region, and prior metastatic chemotherapy status and randomized (1:1) to capecitabine (1000 mg/m^2^ orally twice daily (BID), days 1 to 14 of 21) in combination with sorafenib (orally BID, days 1 to 21, total dose 600 mg/day) or matching placebo. Capecitabine and sorafenib/placebo doses can be escalated to 1250 mg/m^2^ BID and 400 mg BID, respectively, as tolerated, or reduced to manage toxicity. Dose re-escalation after a reduction is allowed for sorafenib/placebo but not for capecitabine. This dosing algorithm was designed to mitigate dermatologic and other toxicity, in addition to detailed guidelines for prophylactic and symptomatic treatment. Radiographic assessment is every 6 weeks for 36 weeks, and every 9 weeks thereafter. The primary endpoint is PFS by blinded independent central review (Response Evaluation Criteria in Solid Tumors 1.1 criteria). Secondary endpoints include overall survival, time to progression, overall response rate, duration of response, and safety. Enrollment began in November 2010 with a target of approximately 519 patients.

**Discussion:**

RESILIENCE will provide definitive PFS data for the combination of sorafenib and capecitabine in advanced HER2-negative breast cancer and better characterize the benefit-to-risk profile.

**Trial registration:**

Clinicaltrials.gov, NCT01234337

## Background

In recent decades, advances in the treatment of metastatic breast cancer (MBC) have provided incremental improvement in disease control and survival [1]. Novel chemotherapies (for example, paclitaxel, capecitabine) for MBC and the introduction of hormone and other targeted therapies (for example, trastuzumab) have corresponded to a steady increase in survival. Despite these improvements, the primary goal of treatment remains palliative with about half of patients succumbing to the disease within 3 years [1-4].

Breast cancer is a heterogenous disease with systemic treatment options primarily based on hormone receptor and human epidermal growth factor receptor 2 (HER2) status, but also emerging therapies that target other molecular pathways involved in development, progression, resistance, and metastasis, such as antiangiogenics and poly(adenosine diphosphate ribose) polymerase (PARP) inhibitors [5]. While management of early disease stages is well defined, management of MBC, particularly HER2-negative disease, is complex as standard treatment strategies are not well established [6,7]. The optimal sequence or combination of agents has not been standardized and is dependent on a variety on intra-patient factors. Combination chemotherapy regimens have been shown to provide clinical benefit in MBC but are associated with significant toxicities and have not shown an overall survival (OS) benefit compared with sequential use of agents [3,8,9]. Novel combinations are needed that improve survival, disease control, and quality of life (QoL) with acceptable toxicity.

Although single-agent use of antiangiogenics has demonstrated only modest efficacy in MBC [10-14], studies in HER2-negative MBC have demonstrated the clinical benefit of adding antiangiogenics to chemotherapy. This was first established with bevacizumab, a monoclonal antibody targeting vascular endothelial growth factor (VEGF), a potent angiogenic factor [15-19]. In the E2100 phase 3 study, the addition of bevacizumab to first-line paclitaxel demonstrated a clinically significant improvement in progression-free survival (PFS) for patients with HER2-negative MBC [16]. PFS increased from 5.9 months for paclitaxel alone to 11.8 months for bevacizumab plus paclitaxel (hazard ratio [HR] = 0.60; 95% confidence interval [CI] = 0.51 to 0.70; *P* < 0.001). The combination was tolerable, although some serious events occurred infrequently. Subsequent studies of bevacizumab in combination with selected chemotherapies have also demonstrated significant improvement in PFS, but the benefit has been notably more modest than the E2100 results [15,18,19]. Furthermore, an OS benefit has not been demonstrated across these bevacizumab studies.

A number of factors might explain the discrepancy between the PFS benefit and the lack of improvement in OS. It is difficult to demonstrate an OS benefit in first-line MBC because treatments after progression likely confound data [20]. In addition, preclinical data suggest that antiangiogenic treatment may result in more aggressive disease at the time of progression, possibly through increased invasiveness of tumor cells and/or by switching to alternative angiogenic pathways to re-establish tumor vascularization [21,22]. This led clinicians to investigate whether other antiangiogenic agents that have a broader spectrum of activity than bevacizumab, such as the tyrosine kinase inhibitors sunitinib and sorafenib, might provide benefit in HER2-negative MBC. While phase 3 studies with sunitinib have been disappointing thus far [10,23-25], a series of phase 2b randomized, placebo-controlled trials have collectively demonstrated sorafenib activity when combined with selected chemotherapies [26-29].

Sorafenib, an oral multikinase inhibitor with both antiproliferative and antiangiogenic activity, is indicated for advanced renal cell and hepatocellular carcinomas [30,31]. Sorafenib targets VEGF receptors-1, -2, and −3, platelet-derived growth factor receptor β, Raf kinase, c-KIT, and Flt-3 [32]. Preclinical data in breast tumor models suggest that adding sorafenib to cytotoxic agents may provide synergistic/additive antitumor effects and may help overcome resistance to cytotoxic agents [33-35].

The Trials to Investigate the Efficacy of Sorafenib (TIES) in Breast Cancer Program was developed to rapidly assess the efficacy and safety of sorafenib in combination with selected systemic therapies for HER2-negative MBC, to determine if phase 3 confirmatory trials should be pursued, and to inform the design of these trials. The TIES program was developed by independent investigators with support from industry to collectively identify settings in HER2-negative MBC where the addition of sorafenib might be of benefit. The program consists of four double-blind, randomized, placebo-controlled, phase 2b screening trials in patients with HER2-negative advanced breast cancer that assessed sorafenib in combination with first- or second-line capecitabine (SOLTI-0701) [26], first-line paclitaxel (NU07B1) [28], first- or second-line gemcitabine or capecitabine (AC01B07) in patients who had progressed during or after a regimen containing bevacizumab [27], and first-line docetaxel and/or letrozole (FM-B07-01) [29]. Two of the TIES programs indicated a potential role for sorafenib in this patient population when used in combination with selected chemotherapies [26,27]. More specifically, results of the SOLTI-0701 supported a phase 3 confirmatory study of the sorafenib-capecitabine combination [26]. AC01B07 also met its primary endpoint, but the PFS benefit with the sorafenib combination was too modest to support a phase 3 trial of similar design [27]. NU07B1 did not demonstrate a statistically significant benefit in PFS with the sorafenib combination but showed a statistically significant improvement in time to progression (TTP) [28]. There was no clinical benefit associated with the sorafenib combination in the FM-B07-01 study [29].

During SOLTI-0701, the addition of sorafenib to first- or second-line capecitabine significantly improved the primary endpoint of PFS compared with placebo (median 6.4 versus 4.1 months; HR = 0.58; 95% CI = 0.41 to 0.81; *P* = 0.001) and the secondary endpoint of TTP (median 6.8 versus 4.1 months; HR = 0.56; 95% CI = 0.39 to 0.80; *P* = 0.001) [26]. There was no significant improvement in overall survival (median 22.2 versus 20.9 months; HR = 0.86; 95% CI = 0.61 to 1.23; *P* = 0.42).

Generally, the combination of sorafenib and capecitabine was manageable, but dose reductions were more common than in the placebo arm [26]. During SOLTI-0701, the starting dose was 1000 mg/m^2^ twice daily (BID) capecitabine (first 14 days of a 21-day cycle) and 400 mg BID (continuously) for sorafenib/placebo. Dose interruptions and reductions were allowed to manage toxicity. Dose reductions in the sorafenib arm were 53% for sorafenib and 78% for capecitabine compared with 14% for placebo and 33% for capecitabine in the placebo arm. The average daily dose of study drugs was lower in the sorafenib arm (mean 584 mg sorafenib and 1461 mg/m^2^ capecitabine) compared with the placebo arm (mean 745 mg placebo and 1839 mg/m^2^ capecitabine). Most patients remained on treatment until disease progression in the sorafenib and placebo arms (63% and 82%), but some discontinued treatment due to adverse events (AEs) (20% versus 9%, respectively). The average duration of treatment in the sorafenib arm was 33.8 weeks for sorafenib and 33.1 weeks for capecitabine, with corresponding values of 22.5 and 22.2 weeks in the placebo arm. The most common toxicity was hand-foot skin reaction (HFSR) associated with sorafenib and hand-foot syndrome (HFS) associated with capecitabine, which occurred more frequently in the sorafenib arm than the placebo arm (90% versus 66% for any grade and 44% versus 14% for Grade 3) and occurred earlier (median time to onset 14 versus 64 days, respectively, for any grade). Other Grade 3/4 events were comparable between the groups.

The results of SOLTI-0701 supported the rationale for a similar confirmatory trial in the phase 3 setting, but also indicated that the study design would require amendments to the dosing schema to address the incidence of HFSR/HFS in addition to more aggressive prevention and management strategies. Here we present the study design of the phase 3 RESILIENCE trial (tRial comparing capecitabinE in combination with SorafenIb or pLacebo for treatment of locally advanced or metastatIc HER2-Negative breast CancEr).

## Methods/design

RESILIENCE is a multinational, randomized, double-blind, placebo-controlled, phase 3 trial designed to assess the efficacy and safety of sorafenib in combination with capecitabine in patients with locally advanced or metastatic HER2-negative breast cancer who received previous treatment with a taxane and anthracycline. The study is being conducted in accordance with Good Clinical Practice guidelines, the guiding principles of the Declaration of Helsinki, and applicable local laws and regulations. The study protocol has been approved by both Regulatory Authorities and internal review boards of the participating centers. All patients will provide written informed consent. The trial is registered at ClinicalTrials.gov (NCT01234337). (For a complete listing of study centers see Additional file 1).

### Patient population and study design

Patients at least 18 years of age with HER2-negative advanced breast cancer who have been treated with a maximum of one prior chemotherapy regimen for metastatic disease are eligible to enroll. Prior treatment with both a taxane and an anthracycline is required, but prior treatment with a VEGF inhibitor (for example, bevacizumab) is not allowed. Table 1 summarizes major eligibility criteria. Patients will be stratified by hormone-receptor status (estrogen and/or progesterone receptor positive versus both negative), geographic region (North America versus Europe versus Other), and number of prior MBC chemotherapy regimens (0 or 1), then randomized (1:1) to receive either sorafenib or placebo in combination with capecitabine (Figure 1).

**Table 1 T1:** Eligibility criteria for RESILIENCE

**Key inclusion criteria**	**Key exclusion criteria**
● Age ≥18 years	● HER2-positive disease
● Life expectancy ≥12 weeks	● Unknown estrogen and progesterone receptor status
● Histologically or cytologically confirmed HER2-negative breast adenocarcinoma	● Previous treatment with a VEGF inhibitor
● Locally advanced (non-resectable) or metastatic disease	● Symptomatic brain metastases
● Measurable or clinically evaluable disease according to Response Evaluation Criteria in Solid Tumors (RECIST 1.1)	● Recent (<4 weeks before entry) major surgery, open biopsy, or significant traumatic injury
● Resistant to or failed prior taxane and an anthracycline or further anthracycline therapy is not indicated	● Uncontrolled hypertension, or active or clinically significant cardiac disease
● No more than one previous chemotherapy regimen for metastatic disease	● Thrombotic, embolic, venous, or arterial events, or other bleeding disorders within the past 6 months
● Prior adjuvant or neoadjuvant chemotherapy allowed	● Any hemorrhage/bleeding event of Grade 3 or above within past 4 weeks
● Prior hormonal therapy for locally advanced or metastatic disease allowed	
● Prior chemotherapy, radiation, or hormonal therapy discontinued ≥4 weeks before randomization; previously irradiated areas must not be the only site of disease	
● ECOG Performance Status of 0 or 1	
● Adequate hepatic and renal function	

*ECOG* Eastern Cooperative Oncology Group, *HER2* human epidermal growth factor receptor 2, *RESILIENCE* tRial comparing capecitabinE in combination with SorafenIb or pLacebo for treatment of locally advanced or metastatIc HER2-Negative breast CancEr, *VEGF* vascular endothelial growth factor.

**Figure 1 F1:**
[figure not shown]
**Study design and treatment schema of RESILIENCE.** *If treatment is well tolerated after Cycle 1; ^†^if sorafenib/placebo 400 mg BID is well tolerated. BID, twice daily; DoR, duration of response; MBC, metastatic breast cancer; ORR, overall response rate; OS, overall survival; PFS, progression-free survival; po, oral; R, randomization; RESILIENCE, tRial comparing capecitabinE in combination with SorafenIb or pLacebo for treatment of locally advanced or metastatIc HER2-Negative breast CancEr; TTP, time to progression.

Patients will receive sorafenib or matching placebo BID on a continuous basis. The initial daily dose of sorafenib is 600 mg taken as one 200-mg tablet in the morning and two 200-mg tablets in the evening. The 600-mg dose was selected because it corresponds to the average daily dose (mean 584 mg/day) in the sorafenib arm of the SOLTI-0701 study [26]. Capecitabine is administered orally on days 1 through 14 of a 21-day cycle at a starting dose of 1000 mg/m^2^ BID. Studies have established the efficacy and safety of capecitabine 1000 mg/m^2^ BID [36]. The daily dose of sorafenib or matching placebo may be increased to 400 mg BID if the 600-mg dose is well tolerated (fatigue, dermatologic toxicities, or gastrointestinal toxicities are no greater than Grade 1) after a 21-day cycle. If the 400-mg BID dose of sorafenib/placebo is well tolerated in a 21-day cycle, then the capecitabine dose may be increased to 1250 mg/m^2^ BID in the subsequent cycle.

### Management of adverse events

Dose reductions, interruptions, and discontinuation of study drugs are required to manage toxicity and are detailed in the study protocol by toxicity type and grade, which also specifies how dosing of the study drug(s) should be modified. Re-escalation of sorafenib/placebo after a dose reduction is permitted per protocol guidance, but dose re-escalation is not permitted for capecitabine as per the capecitabine label. If an AE leads to dose interruption of more than 21 days, recurs too frequently and leads to dose reductions, and/or is too severe (for example, Grade 4 non-hematologic toxicities), one or both study drugs may be permanently discontinued. Sorafenib treatment cannot be continued if capecitabine has been discontinued permanently, but capecitabine may continue if sorafenib has been permanently discontinued. Proactive management of HFSR/HFS leads to better management of these toxicities, allowing patients to remain on treatment. Based on the experience in the SOLTI-0701 study, the RESILIENCE protocol includes comprehensive guidelines for prophylactic management (for example, pedicure and moisturizing creams) and symptomatic treatment (for example, topical exfoliants and analgesics) of HFSR/HFS (Table 2), in addition to dose modifications of study drugs.

**Table 2 T2:** Recommended prevention/management strategies for skin toxicities consistent with hand-foot skin reaction/hand-foot syndrome

**Toxicity grade**	**Practical prevention/management strategies for HFSR/HFS**
Grade 0 (preventive strategies)	● Maintain frequent contact with trial physician to ensure early diagnosis of HFSR
	● Practical prevention strategies
	○ Pedicure by a podiatrist for subjects with pre-existing hyperkeratosis
	○ Subjects should avoid hot water, and clothing or activities that can cause friction on the skin
	○ Moisturizing cream should be applied sparingly
	● Padded gloves and open shoes with padded soles should be worn to relieve pressure points
Grade 1 any occurrence	● Continue preventive strategies and in addition:
	○ Soak hands in cool water
	○ Apply petroleum jelly to moist skin
	● In the case of hyperkeratotic lesions, exfoliate the hands or feet and apply moisturizing cream immediately afterwards
Grade 2 or 3 any occurrence	● Continue supportive/management measures and add analgesic(s) for pain
	● Dose modifications to study treatments per protocol guidance

*HFS:* hand-foot syndrome, *HFSR:* hand-foot skin reaction.

### Assessments

Electrocardiogram, blood tests, patient QoL questionnaires, a complete physical examination, and assessment of Eastern Cooperative Oncology Group (ECOG) performance status will be performed at the beginning of each treatment cycle. On a weekly basis during the first 6 weeks of treatment, patients will undergo a brief physical examination comprising assessment of vital signs and a thorough dermatologic examination for HFSR/HFS and other dermatologic toxicities.

Tumor measurements during the study will be conducted using computed tomography scan and/or magnetic resonance imaging, with a bone scan if clinically indicated at the time of screening, on day 1 of Cycle 1 and every 6 weeks from the day of randomization through week 36, and then every 9 weeks thereafter. Treatment response will be evaluated using Response Evaluation Criteria in Solid Tumors (RECIST 1.1) criteria [37].

### Study endpoints

#### Primary and secondary endpoints

The primary efficacy endpoint is PFS by blinded independent central review. Secondary efficacy endpoints are OS, TTP, overall response rate (ORR), and duration of response (DoR). Safety evaluations comprise AE reporting by standard methods (National Cancer Institute-Common Terminology Criteria for Adverse Events v4.0) and assessment of laboratory abnormalities.

#### Patient-reported outcomes

Patient-reported outcomes (PROs) include an evaluation of breast cancer symptoms using the Functional Assessment of Cancer Therapy-Breast Symptom Index (8 items) (FBSI-8 questionnaire) [38,39] and health-related quality of life (HRQoL) using the EuroQoL 5-Dimension Questionnaire (EQ-5D) [40].

#### Pharmacokinetics

Pharmacokinetic analysis of capecitabine, 5-fluorouracil (5-FU) (the active metabolite of capecitabine), and sorafenib exposures will be conducted. Five blood samples each will be collected from approximately 200 patients for these analyses. On day 14 of Cycle 2, samples will be obtained prior to and at 0.5, 1, 2, and 4 hours after the capecitabine dose to estimate capecitabine and 5-FU exposure. Sorafenib exposure will be estimated from a single blood sample on day 14 of Cycle 2.

#### Exploratory biomarkers

Exploratory analyses of cancer biomarkers such as PIK3CA, BRAF, and KRAS will be performed to possibly identify subpopulations of patients with differential response to sorafenib treatment. Plasma samples for biomarker analysis (genetic and non-genetic) will be collected at screening, prior to drug administration in Cycles 1 through 3, and at the end of treatment. Permission to obtain an archived biopsy sample from diagnosis or later will be sought from all patients during screening.

### Statistical analyses

Assuming a 1-sided alpha of 0.005, a power of 98.9%, and a randomization ratio of 1:1 between the sorafenib and placebo groups, 363 events are required to detect a 66.7% increase in PFS. Assuming enrollment at a rate of 20 patients per month, an enrollment ramp-up time of 4 months, a dropout rate of 10%, an exponentially distributed event time, 4.5-month median PFS for the control group, and a 28.4-month enrollment period, a sample size of 519 is estimated with an expected trial duration of 31.4 months.

Efficacy analyses will be performed with the intent-to-treat population. The primary analysis of the study will be performed after approximately 363 PFS events. Analysis of PFS will be performed using a log-rank test, stratified by randomization factors (that is, hormone-receptor status, geographic region, and prior chemotherapy for MBC) with 1-sided alpha of 0.005. All secondary time-to-event endpoints (OS, TTP and DoR) will be analyzed in a similar manner but with a 2-sided alpha of 0.05.

Assuming a median OS of 12 months for the control group, approximately 270 deaths would be expected at the time of the primary analysis of PFS, at which time an interim analysis of OS is planned. For the final analysis of OS, 405 deaths are projected to occur by approximately 47.9 months after the first patient is randomized. Analysis of 405 events will provide 82% power to detect a 33.3% increase in survival with sorafenib compared with placebo with a 2-sided alpha of 0.05, assuming one interim analysis of OS at the time of the PFS analysis. The interim and final analyses of OS will be performed using an O’Brien-Fleming type alpha spending function.

For other endpoints, a Cochran-Mantel-Haenszel test with the randomization factors as strata will be used to compare ORR between treatment arms. PROs will be analyzed by time-adjusted area under the curve with the comparison between treatment arms made using a covariance analysis, if appropriate. The predictive value of baseline biomarker levels (genetic and non-genetic) for the treatment effect in PFS and OS will be assessed using appropriate statistics to determine whether any of the known biological targets of sorafenib are important in assessing efficacy. In addition, correlations between change in biomarker levels from baseline and PFS and OS will be investigated.

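### Duration of response is assigned a between-arm log-rank test, but only responders have a duration, so its p-value is not a randomised comparison (minor)

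*Protocol article*

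**What the plan says.** The Protocol article, under Primary and secondary endpoints, lists DoR last among four: "Secondary efficacy endpoints are OS, TTP, overall response rate (ORR), and duration of response (DoR").

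Under Statistical analyses it sets the primary test: "Analysis of PFS will be performed using a log-rank test, stratified by randomization factors". It then carries that method over to the secondary time-to-event "endpoints (OS, TTP and DoR) will be analyzed in a similar manner", with a two-sided alpha of 0.05. The general population statement is "Efficacy analyses will be performed with the intent-to-treat population". Response itself is compared separately: "a Cochran-Mantel-Haenszel test with the randomization factors as strata will be used to compare ORR between treatment arms".

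The article does not define DoR, does not limit it to description, and gives no version of it that covers every randomised patient.

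**The concern.** OS and TTP can be measured from randomisation in every patient. DoR, as the term is ordinarily used, starts at response, so a non-responder has no value. A log-rank test of DoR can only be run among responders, a group selected after randomisation by an outcome that sorafenib may change. The plan allows for such a change, since it tests ORR between the arms.

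Suppose sorafenib turns some non-responders into short-lived responders. They join the sorafenib responder group and have no counterpart in the placebo group. The sorafenib curve then falls faster although nobody's response became shorter. In principle the reverse also holds: a treatment that loses its weaker responders would seem to prolong response.

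Because the article names DoR and gives it a test and an alpha, this is a stated analysis choice and not a detail left to the SAP. What is at stake is a p-value below 0.05 that could be taken as randomised evidence on durability.

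**Working it through.** **1. The plan's own figures.** None of them depends on the DoR test, but they were checked to see whether the design is otherwise affected. The plan states "Assuming a 1-sided alpha of 0.005, a power of 98.9%, and a randomization ratio of 1:1" and "363 events are required to detect a 66.7% increase in PFS", that is HR = 1/1.667 = 0.60.

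Events = 4(z₀.₉₉₅ + z₀.₉₈₉)² / (ln 0.60)² = 4(2.576 + 2.290)² / 0.2609 = 363. This reproduces the plan.

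For OS, 405 deaths at HR 0.75 and two-sided 0.05 give 82.5% power without an interim look, and 82.0% with one O'Brien-Fleming-type look at 270 of 405 deaths. The stated 82% is reproduced.

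**2. How the bias arises.** These inputs are assumed, because the article gives no ORR or DoR. Thirty per cent of patients would respond on either arm, with median DoR 8 months and no treatment effect on duration. Sorafenib adds 10 points of responders with median 4 months. Durations are exponential.

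- Responders with about 260 patients per arm: placebo 0.30 × 260 = 78; sorafenib 0.40 × 260 = 104, of whom 26 (25%) are added.
- The sorafenib responder curve is 0.75·2^(−t/8) + 0.25·2^(−t/4). With x = 2^(−t/8), the median solves 0.75x + 0.25x² = 0.5, so x = (−3 + √17)/2 = 0.562 and t = −8·log₂(0.562) ≈ 6.7 months.
- With 15 points added, the weights are 2/3 and 1/3. Then x = −1 + √2.5 = 0.581 and t ≈ 6.3 months.

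The apparent fall from 8 months to 6.7 or 6.3 comes entirely from who is counted.

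**3. Size of the error.** Simulated trials of 519 patients, 1:1, unstratified log-rank among responders, two-sided 0.05, no censoring, 3,000 runs each. Of the patients, 30% respond on either arm with median 8 months.

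| Added responders on sorafenib | Significant against sorafenib | Significant for sorafenib |
|---|---|---|
| none | 2.8% | 2.8% |
| 10 points, median 8 months | 2.4% | 3.0% |
| 5 points, median 4 months | 6.8% | 0.9% |
| 15 points, median 6 months | 8.3% | 0.5% |
| 10 points, median 4 months | 12.9% | 0.2% |
| 15 points, median 4 months | 24.3% | 0.1% |
| 15 points, median 3 months | 31.9% | 0.03% |

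Each tail is nominally 2.5%. Simulation error is about √(0.025 × 0.975/3000) = 0.3 points near nominal and √(0.14 × 0.86/3000) = 0.6 points near 14%.

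**4. With censoring (uniform, 3 to 28 months), with and without stratification.** Repeated runs gave:

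- ORR 25% vs 35%, added responders at 4 months: apparent HR about 1.2; 14 to 15% unstratified and about 14% over 12 strata.
- ORR 30% vs 40%, added responders at 3 months: apparent HR about 1.23 to 1.25; 21 to 22% unstratified and 20 to 21% stratified.
- 10 points added at 6 months: HR about 1.08 and about 6%.
- Identical arms: 2.6% unstratified and 2.2% stratified.

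**5. A true benefit can be hidden.** Suppose sorafenib lengthens DoR by 10% in patients who respond on either arm, and adds 15 points of responders at 4 months. The statistic still favours placebo in 76% of runs, significantly so in 10%. With a 20% lengthening the figures are 61% and 4.8%.

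**The case against.** The strongest reply concerns weight. DoR is the last of four secondary endpoints, and no sample size, power or decision depends on it. ORR, PFS and TTP are all compared over randomised patients, so an imbalance in response would be visible beside any DoR result. The article does not say that a DoR p-value will support a claim. All of this stands, and it is why the point is minor.

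It is also fair that every rate above is assumed and that the bias is conditional. If the response rates are equal, or added responders resemble the others, the test keeps its nominal error. The range therefore has to be shown from its lower end.

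Three stronger readings are tempting, and the documents do not support them.

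- *The test will be biased against sorafenib.* The article gives no response rate or DoR by arm, so neither the presence nor the direction of bias is known. The opposite case, where sorafenib loses weak responders and looks better, has no support in the text and was not quantified.
- *Stratifying by 3 × 2 × 2 = 12 cells breaks the test among so few responders.* The stratified and unstratified rejection rates were nearly the same, and with equal durations the stratified test rejected 3.1% and 2.2% in its two tails.
- *The intent-to-treat sentence contradicts the DoR analysis.* It is a general statement in a condensed article. The natural reading for DoR is responders within that population.

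What the reply does not remove is the named test with its alpha.

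**Conclusion.** The point holds as a minor one. The article commits DoR to a between-arm stratified log-rank test that can only be run in responders, so randomisation does not protect the comparison and the p-value does not measure a treatment effect on durability.

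Under the assumed inputs (25 to 30% responding on either arm, median 8 months), a falsely significant result against sorafenib occurs with these probabilities:

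- nominal 2.5% if added responders have the same durations;
- about 6 to 8% with 5 points added at 4 months, or 10 to 15 points at 6 months;
- about 13 to 22% with 10 points added at 3 to 4 months;
- about 24 to 32% with 15 points added at 3 to 4 months.

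The conclusion rests on the ordinary meaning of DoR, since the article gives no definition. If the full protocol defines it over all randomised patients, the point falls away. The PFS and OS designs are untouched.

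**What to change.** Remove DoR from the sentence that extends the log-rank test to the secondary endpoints, leaving OS and TTP. Add that DoR will be summarised by arm among responders with a Kaplan-Meier median and confidence interval, labelled descriptive and conditional on response, without a between-arm p-value.

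If an arm comparison is wanted, compare mean time in response, or the probability of being in response over time, across all randomised patients, with non-responders counted as zero.

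The cost is one sentence, the loss of the DoR p-value and, if chosen, one small analysis from data already collected. No patient number or event count changes.
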